# **<Overview>**

| **Study title** | Pre-surgical Aspirin Administration for the Prevention of Thromboembolic Complications of Coil Embolization for Ruptured Aneurysms  (ASTOP study) |
| --- | --- |
| **Purpose of the study** | During endovascular treatment of ruptured cerebral aneurysms, thromboembolisms are known as uncontrollable therapeutic complications, and further improvement of treatment outcomes can be expected by controlling these complications. We hypothesized that the administration of preoperative antiplatelet agents for endovascular treatment may reduce thromboembolic complications.  The patients who are planned to undergo endovascular treatment for acute ruptured saccular cerebral aneurysms will be randomly assigned to receive aspirin or placebo preoperatively. The incident rate of intraoperative thromboembolic events, postoperative new neurological dysfunction, new cerebral infarction in postoperative magnetic resonance imaging (MRI), perioperative cerebral ischemic events or all hemorrhagic events, and mRS at 3 months will be compared between the two groups. |
| **Study Design** | A multicenter, randomized, double-blind, placebo-controlled study |
| **Phase** | Confirmatory study |
| **Test drug** | Generic name: Aspirin  Dosage form: Powder  Storage conditions: Storage at room temperature |
| **Inclusion criteria** | Patients who meet all of the following criteria   1. Patients with ruptured cerebral aneurysms in the acute phase 2. Patients scheduled for aneurysm embolization within 72 h of onset 3. Patients aged 20 years or older at the time of presentation 4. Patients for whom written informed consent has been obtained from the person or their legally acceptable representative (e.g., spouse, parent, adult child) for participation in the study. |
| **Exclusion criteria** | Patients who meet any of the following criteria   1. Pre-stroke mRS ≧ 4 2. Patients with dissecting cerebral aneurysms in whom parent vessel occlusion was attempted 3. Patients with ruptured recurrent aneurysms after cerebral aneurysm coil embolization 4. Patients with ruptured cerebral aneurysms associated with cerebral arteriovenous malformations, moyamoya disease, or infectious cerebral aneurysms 5. Patients treated simultaneously for two or more aneurysms 6. Patients already taking antiplatelet drugs 7. Patients with a history of allergy to lactose, aspirin, or salicylic acid preparations 8. Patients who cannot undergo MRI 9. Patients with contraindications to aspirin 10. Patients who are considered inappropriate for participation in the study by the treating physician |
| **Endpoint** | **Primary outcomes**   1. Incidence rate of intraoperative thromboembolic complications 2. Incidence rate of symptomatic ischemic lesions on MRI diffusion-weighted imaging (DWI) evaluated by Independent Review Committee (IRC)   **Key secondary outcomes**   1. Incidence rate of all bleeding events within 14 days of enrollment 2. Incidence rate of cerebral ischemic events in the first 14 days after MRI   **Other secondary outcome**   1. Incidence rate of symptomatic ischemic lesions in MRI-DWI evaluated by INV 2. mRS score at 3 months   **Exploratory outcomes**   1. Number and size of ischemic lesions in MRI-DWI evaluated by the IRC and INV 2. Incidence rate of cerebral hemorrhage along the tube tract for ventricular drainage on computed tomography (CT) scans in the first 14 days after endovascular treatment (EVT). |
| **Research methods** | Patients who are scheduled for coil embolization for a single intracranial aneurysm, presumed to be the rupture site, within 72 h of the onset of subarachnoid hemorrhage and have provided written informed consent to participate in this study will be divided into the following two groups using an Interactive Web Response System (IWRS).  [Aspirin group].  Aspirin 200mg will be administered via a nasogastric tube after induction of general anesthesia prior to embolization.  [Placebo group].  Placebo (lactose) will be administered via a nasogastric tube after induction of general anesthesia before embolization. |
| **Target number of research participants** | 484 patients (242 in each group) |

| **Management of Samples and Information** | The sample and information shall be stored for 10 years in a key archive of the Department of Endovascular Surgery by [name], and then dissolved and discarded so that personal information cannot be identified. |
| **Ethical guidelines** | All persons involved in the study follow the spirit of the Declaration of Helsinki of the World Medical Association (revised October 2013), as well as the Clinical Research Act (Act No. 16 of 2017) and the Enforcement Regulations of the Clinical Research Act. |
| **Certified Clinical Research Review Board** | Before conducting this study, the Certified Clinical Research Review Board will review the ethical, scientific, and medical relevance of this study. This study will be conducted after being registered with jRCT after obtaining approval from the Certified Clinical Research Review Board and with permission from the administrators of the participating medical institutions. If the results of deliberation by the Certified Clinical Research Review Board are "continued," the Study Protocol or Case Report Form (CRF), informed consent form, etc. will be revised based on the results of the deliberation, approved, and the above procedure will be carried out, followed by the present study. In addition, the Certified Clinical Research Review Board continuously reviews whether the study has been properly conducted at least once a year. |
| **Research points**  **Summary** | ・Collection of human specimens □ Yes ■ No  ・Monitoring ■ Yes □ No  (Monitoring: Health Science R&D Centre, Tokyo Medical and Dental University, Tokyo, Japan)  ・Audit □ Yes ■ No  ・Invasion □ Yes ■ With slight invasion □ No  ・Multicenter collaborative research □Tokyo Medical and Dental University only ■ Multicenter principal □ Multicenter sharing  ・Samples and information received from other facilities ■ Yes □ No  ・Provision of samples and information overseas □ Yes ■ No  ・Location of Samples, Information, Records, etc.: Department of Endovascular surgery office  ・Storage manager : [name]  ・Storage period: 10 years  ・Discard method: When information needs to be discarded, eliminate the data from the stored computer, treat the output of the print, etc. with a shredder, etc. to discard it.  ・Secondary availability ■ Yes □ No  ・Storage of records of provision  ■ Described in this document □ Described in attached sheet □ MTA □ Not applicable  ・Rewards  □ Yes ■ None  ・Anonymization method: Corresponding table  ・Compensation insurance　 ■ Yes □ No  ・Research fund: ■ Operating expenses □ Grants-in-Aid for Scientific Research ■ Subsidies other than Grants-in-Aid for Scientific Research ■ Donations □ Contract and collaborative research |

#

# **1.** **Study Background**

Endovascular treatment (EVT) has become an established treatment for cerebral aneurysms ^1, 2^. However, EVT has a potential risk of thromboembolic complications because it involves inserting a foreign body into the body ^3, 4^. Dual antiplatelet therapy with aspirin and clopidogrel is a common EVT for unruptured cerebral aneurysms that prevents thrombotic complications ^5^. This dual antiplatelet therapy has enabled the use of useful devices such as stenting and balloons, which are support devices for coil embolization or flow diverter placement, as well as the treatment of complex forms of aneurysms with a high degree of difficulty that has been previously difficult to treat ^6-8^.

EVT for ruptured cerebral aneurysms is associated with a high incidence of intraoperative thromboembolism because of hypercoagulable state as a bioprotective response to subarachnoid hemorrhage (SAH) ^9, 10^. Cognard et al. reported complications in 13.3% of cases and severe neurological sequelae or death in 4.2%^11^. Therefore, controlling thromboembolic complications is important in the EVT of ruptured cerebral aneurysms.

In 2006, Rie et al. reported that the administration of antiplatelet agents during EVT for ruptured cerebral aneurysms reduces thromboembolic morbidity^12^. However, in 2009, a subanalysis of the International Subarachnoid Aneurysm Trial (ISAT), a randomized controlled trial (RCT) of craniotomy versus EVT for ruptured cerebral aneurysms, reported that intraoperative or postoperative antiplatelet use in EVT for ruptured cerebral aneurysms did not improve SAH outcomes. The biggest problem with this study was that the antiplatelet agents were administered either intraoperatively or postoperatively, meanwhile, they should have been administered preoperatively as antiplatelet agents to prevent thrombus formation during treatment. Recently, the usefulness of preoperative administration of antiplatelet agents to prevent thromboembolism complications in EVT in the acute stage for ruptured cerebral aneurysms has been reported ^6, 14^. Increased bleeding complications are a concern when administering antiplatelet agents, which may promote bleeding in the acute phase of a ruptured cerebral aneurysm. In addition to the risk of aneurysmal rebleeding, those with ruptured cerebral aneurysms have a potentially intrinsic risk of hemorrhagic complications, including the risk of gastrointestinal bleeding resulting from increased intracranial pressure associated with SAH; the risk of hemorrhagic complications during additional surgical treatments such as ventricular or spinal drainage, which may be required if acute hydrocephalus is complicated; and the risk of increased intracerebral hematoma. However, in previous retrospective studies on preoperative and intraoperative antiplatelet administration in EVT for ruptured cerebral aneurysms, hemorrhagic morbidity has not increased, and the safety of its use^6, 12^.

Thus, although the usefulness and safety of preoperative antiplatelet therapy for the EVT of ruptured cerebral aneurysms in the acute phase have been reported, they have not been tested in an RCT. Therefore, in this study, among patients scheduled for EVT during the acute phase (within 72 h of onset) for ruptured cerebral aneurysms, consented patients will be randomly assigned double-blindly to receive aspirin 200 mg via a nasogastric tube or placebo after induction of general anesthesia before EVT. To evaluate the occurrence of intraoperative thromboembolic complications and the presence or absence of concordant neurological dysfunction on MRI DWI taken within 6-48 h after surgery, global cerebral ischemic events within 14 days after MRI, all hemorrhagic events within 14 days of enrollment, and mRS at 3 months. This study aimed to determine the safety and efficacy of preoperative aspirin administration in the EVT of acute-phase ruptured cerebral aneurysms.

# **2.** **Purpose of the study**

　During EVT of ruptured cerebral aneurysms, thromboembolic complications are known to be uncontrollable therapeutic complications and further improvement in treatment outcomes can be achieved by controlling these complications. We hypothesized that the administration of preoperative antiplatelet agents for EVT may control thromboembolic complications.

　For embolization of acutely ruptured saccular cerebral aneurysms, patients will be randomized to receive aspirin or placebo preoperatively to test for differences in the incidence rate of intraoperative thromboembolic events, new postoperative neurological dysfunctions, new cerebral infarctions on postoperative MRI, perioperative cerebral ischemic events, any hemorrhagic events, and 3-month mRS between the two groups.

# **3.** **Summary of Drugs Used in Clinical Research**

When performing embolization of a ruptured cerebral aneurysm, a nasogastric tube will be inserted after the induction of general anesthesia, and 200 mg of aspirin powder or 200 mg of placebo-lactose will be dissolved in approximately 20mL of tepid water via a nasogastric tube.

・Aspirin (Aspirin)

Date of approval: August 6, 1985

　Approval Number: 16000AMZ03805000

　The products were manufactured and marketed by Mylan Pharmaceutical Co. Ltd.

　Sales: Pfizer Pharmaceuticals Inc.

　Dosage form: Powder (crystals)

　Storage: Storage at room temperature

・Lactose (Lactose Hydrate)

Manufacturing approval Date: February 1, 2008

Approval Number: 27A2X00206

Manufactured and marketed by Mylan Pharmaceutical Co., Ltd.

　Sales: Pfizer Pharmaceuticals Inc.

Dosage form: Powder (crystals)

　Storage: Storage at room temperature

# **4. Patient population**

## **4-1.** **Inclusion criteria**

**The study will be conducted on patients who meet all of the following conditions.**

1. Patients with ruptured cerebral aneurysms in the acute phase
2. Patients scheduled for aneurysm embolization within 72 h of onset
3. Patients aged 20 years or older at the time of presentation
4. Patients for whom written informed consent will be obtained from the participants or their legally acceptable representatives (e.g., spouse, parent, or adult child) for participation in the study.

[Rationale] 1), 2), 3) Basic target diseases and appropriate timing of treatment.

4) Consent from the person is desirable, but owing to the nature of the disease, which is often accompanied by a disturbance of consciousness, consent from a legally acceptable person qualifies the participant.

## **4-2. Exclusion criteria**

**Exclude patients who meet any of the following criteria**

1) Individuals without independent premorbid activities of daily living (pre-stroke mRS ≧4).

2) Patients with dissecting cerebral aneurysms in whom parent artery occlusion was attempted

3) Patients with recurrent ruptured cerebral aneurysms after cerebral aneurysm coil embolization

4) Patients with cerebral arteriovenous malformations, moyamoya disease, and other cerebral aneurysms or ruptured infectious cerebral aneurysms

5) Patients treated simultaneously for two or more aneurysms

6) Patients already taking antiplatelet drugs

7) Patients with a history of allergy to lactose, aspirin, or salicylic acid preparations

8) Patients who cannot undergo MRI

9) Patients with contraindications to aspirin

10) Other patients considered by the treating physician not appropriate to participate in the study

[Rationale Setting] 1), 2), 3), 4), 5), 6) Effect on Evaluation of Efficacy

　　　　　　　　 　7), 8), 9), 10) For safety considerations

# **5.** **Method of obtaining consent from the patients**

Before the study, the investigator or sub-investigator in each collaborative study period (each participating institution) will provide the patients scheduled for EVT for a ruptured cerebral aneurysm and their legally acceptable representative with an easy-to-understand explanation of the study. Using the latest informed consent form approved by the Certified Clinical Research Review Board preoperatively, written informed consent to participate in the study will be obtained. When obtaining consent, sufficient time and opportunity to ask questions about participating in the study will be provided. All questions will be sufficiently answered. The principal investigator or physician responsible for the explanation will confirm whether the subject or his/her legally acceptable representative fully understands the content of the information and agrees with it. The investigator or sub-investigator shall enter the date of explanation on the informed consent form and sign the form with or without a seal. The participant or his/her representative shall fully understand the contents of the written information, agree with the date of consent, and affix his/her name and seal or signature to the written agreement.

The investigator or sub-investigator shall supply the participant or his/her legally acceptable representative with a copy of the signed and sealed consent form and retain the original consent form at the relevant medical institution.

In the event of a decision to continue participating in the study, the investigator or sub-investigator shall revise the explanatory documents and re-explain to the participant using the revised explanatory documents. Consent for the continuation of the study will be obtained from the participants or the legally acceptable representatives of their free will.

When a participant or a legally acceptable representative offers withdrawal of consent, this shall be noted in the medical records. The participant or the legally acceptable representative will sign the consent withdrawal form, and the principal investigator or sub-investigator will sign the date of confirmation and name and seal. The investigator or sub-investigator shall supply the participants or their proxies with a copy of the signed and sealed consent withdrawal form, and the original consent withdrawal form will be retained at the relevant medical institution.

# **6.** **Methods of Research (Content)**

This will be a double-blind, parallel-group study to test the efficacy and safety of aspirin in patients with ruptured cerebral aneurysms who will be randomly assigned to receive aspirin or a placebo before EVT. The following diagram describes the procedure of this study, the decision of the diagnosis and treatment plan of the ruptured cerebral aneurysm case recommended in this study, a technique of EVT, correspondence in the thrombosis generation during the operation, and postoperative management.

**Schema of the study**

**
[figure not shown]
**

**Diagnosis and treatment decision of ruptured cerebral aneurysm.**

　After diagnosing subarachnoid hemorrhage by head CT/MRI, the site and configuration of the ruptured cerebral aneurysm are evaluated by computed tomography angiography/magnetic resonance angiography to identify the ruptured site. The patient's condition, including neurologic findings, vital signs, hematologic tests, chest CT and radiography, and electrocardiographic findings at the time of the visit, will be assessed, and the treatment plan will be decided in the department. If EVT is planned, it will be considered that the patient meets the inclusion criteria and does not meet the exclusion criteria. If consent is obtained from the patient or a relative, the patient will be enrolled and assigned. Patients will be provided systemic management, including sedation and antihypertensive agents, and will await surgery. Preoperative systemic management, including antihypertensive and sedative methods, and management of hydrocephalus (whether CSF drainage is performed preoperatively or postoperatively) are left to each institution.

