**Endovascular treatment technique and intraoperative response to thrombus.**

　Cerebral aneurysm embolization with EVT within 72 h of presentation. EVT is performed under general anesthesia. Administration of a specified number of drugs (aspirin 200 mg or lactose 200 mg) at the time of enrollment/allocation will be performed by the physician in charge of anesthesia or the study sub-investigator via the gastric tube after induction of general anesthesia. The surgeon group will not be administered any visible medication. A cerebral aneurysm embolization will be performed.

Cerebral aneurysm embolization is performed via the transfemoral, radial, brachial, and carotid arteries and a guiding catheter is placed in the internal or vertebral carotid artery. Intraoperatively, heparin, an anticoagulant, is administered intravenously at the discretion of the surgeon, and systemic heparinization is performed to activate coagulation time (ACT) from 250 s to 300 s. A microcatheter and microguidewire are used to place the microcatheter in the aneurysm. A coil for aneurysm embolization is placed in the aneurysm via a microcatheter placed in the aneurysm. If needed, a distal access catheter that allows stable distal vascular access, balloon catheter neck modeling, and double-catheter embolization with two microcatheters may be used. Treatment is terminated when sufficient embolization is achieved to prevent aneurysm re-rupture.

Intraoperatively, if there is evidence of cerebral angiographically evident thrombosis around the aneurysmal neck or in the parent artery (primary endpoint 1), ACT will be measured again immediately, and heparinization will be intensified to provide an ACT > 300 s, or Ozagrel Sodium 80 mg administered intravenously. To confirm the resolution of the thrombus, repeat angiography will be performed as appropriate. If there is a tendency to exacerbate the thrombus, endovascular procedures such as thrombus disruption with a balloon catheter and thrombus retrieval with a stent retriever or thrombus aspiration catheter should be considered. When required, the emergency key of the case will be opened to check the details of the drug administered promptly; if the drug administered is aspirin powder 200 mg, clopidogrel 300 mg will be administered, or if the drug administered is lactose 200 mg, aspirin powder 200 mg and clopidogrel 300 mg will be administered via a nasogastric tube.

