# **7.** **Endpoint**

## **7-1.** **Items related to the evaluation of efficacy**

　Primary outcomes

1) Incidence rate of intraoperative thrombotic complications

It is defined as the proportion of patients with evidence of cerebral angiographically evident thrombus formation in the vicinity of the aneurysm neck or parent artery during surgery.

2) Incidence rate of symptomatic ischemic lesions on MRI diffusion-weighted imaging (DWI) evaluated by the Independent Review Committee (IRC)

It is defined as the percentage of patients with acute-phase ischemic lesions on MRI-DWI performed 6–48 h postoperatively and with concordant neurologic findings.

Key secondary outcomes

1) Incidence rate of all bleeding events within 14 days of enrollment

As a basic protocol, a head CT is performed within 48 h postoperatively and at 14±2 days postoperatively. Additionally, imaging evaluations were conducted as required. The incidence rate of all bleeding events is defined as the percentage of patients with a ruptured aneurysm (symptomatic subarachnoid or intracerebral hemorrhage due to rupture of an aneurysm of interest), a hemorrhagic stroke (symptomatic subarachnoid and intracerebral hemorrhage not due to rupture of target aneurysm, or the proportion of patients who experienced "major hemorrhage" according to ISTH criteria within 14 days post-registration.

2) Incidence rate of cerebral ischemic events in the first 14 days after MRI

The basic protocol is head CT performed within 6–48 h after surgery and 14 ± 2 days after surgery. This is defined as the percentage of patients with transient ischemic attack within 14 ± 2 days after MRI (neurological symptoms lasting less than 24 h with or without imaging findings) or ischemic stroke (focal neurological symptoms lasting more than 24 h and ischemic lesions confirmed by head CT or MRI) during the study period.

Other secondary outcomes

1) Incidence rate of symptomatic ischemic lesions in MRI-DWI evaluated by INV.

2) mRS at 3 months

Assessment is based on mRS scoring 3 months after the onset of subarachnoid hemorrhage.

　Exploratory outcomes

1) Ischemic lesions on MRI-DWI (number and size: 0–4 mm, 5–9 mm, 10–14 mm, 15 mm or greater, categorized as IRC or INV)

2) Incidence rate of cerebral hemorrhage along the tube tract for ventricular drainage on CT scans in the first 14 days after EVT.

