## **14-1. Full analysis set**

　　The definitions of the analyzed population are as follows:

　Intention-to-treat (ITT) Group

All randomized populations will be included.

・Modified intention-to-treat (mITT) group

Patients in the ITT population excluded: ① patients who had never received a treatment either aspirin or placebo; ② patients who did not have any post-randomization data; and ③ patients who met the well-defined and objectively determinable criteria for selection and exclusion.

・Safety analysis set (Safety Analysis Set; SAS)

The study population will be randomized and will receive the treatment (aspirin or placebo).

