**Analysis of the key secondary endpoints**

1) Incidence of all bleeding events within 14 days of onset

2) Incidence of global cerebral ischemic events in the first 14 days after MRI radiography after surgery

For mITT, the number and percentage of patients with events will be calculated in each group, and the difference in the percentage between the two groups (aspirin-placebo group) and the 95% confidence interval will be calculated. If the upper limit of the confidence interval was less than 10%, non-inferiority was demonstrated. Comparisons between the groups for each endpoint will be based on the closed test procedure described above.

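### The bleeding endpoint has three different start points, and two of them count bleeds before the only dose in the 10-point non-inferiority test

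*Protocol*

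**What the plan says.** **Allocation and dose.** In section 6 (diagnosis and treatment decision), after consent "the patient will be enrolled and assigned. Patients will be provided systemic management, including sedation and antihypertensive agents, and will await surgery". Entry requires "Patients scheduled for aneurysm embolization within 72 h of onset". The one dose of aspirin or placebo is given "via the gastric tube after induction of general anesthesia" (section 6, endovascular technique).

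**Start of the bleeding window.** The protocol gives three anchors for the first key secondary outcome:

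- Enrollment or registration. The Overview has "Incidence rate of all bleeding events within 14 days of enrollment", and section 7-1 repeats it and adds "according to ISTH criteria within 14 days post-registration". Section 1 and the postoperative-management text in section 6 also use enrollment.
- Onset. The analysis text in section 14-3 has "Incidence of all bleeding events within 14 days of onset".
- Surgery. The event definitions in section 8 confine stroke events to the period from surgery to 14 ± 2 days afterwards, and define both aneurysm rupture and hemorrhagic stroke as postoperative. The list of ISTH major bleeds that follows has no such limit.

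Section 7-1 includes "symptomatic subarachnoid or intracerebral hemorrhage due to rupture of an aneurysm of interest" without a post-dose or post-surgery condition.

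**Analysis.** Section 14-3 tests non-inferiority in the mITT set: the upper 95% limit for aspirin minus placebo must lie below 10%. Section 14-1 removes from that set "patients who had never received a treatment either aspirin or placebo". Section 9-1 foresees re-rupture between allocation and embolization that leads to surgery being abandoned.

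**The concern.** If the window opens at enrollment or onset, it opens before either arm has received anything. A re-rupture while the patient waits, or a qualifying bleed from preoperative drainage (which section 6 leaves to each institution), is then scored as trial bleeding although it says nothing about aspirin. Whether it is scored also depends on a later surgical decision: if the patient is embolized and dosed it is an mITT event, and if surgery is cancelled the patient leaves the set. Under the section 8 definitions, the same rupture would not count in either case.

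This is the protocol's only formal decision rule on bleeding. Events unrelated to treatment, equally frequent in both arms, pull the risk difference toward zero, which makes a false claim of non-inferiority more likely. They also widen the interval, which lowers the chance of a correct claim. And because the anchors conflict, two analysts could count different events from the same data.

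**Working it through.** **1. Side by side.** Take a patient who re-bleeds symptomatically after allocation and before induction.

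| Anchor | Surgery goes ahead, patient dosed | Surgery cancelled, never dosed |
|---|---|---|
| Enrollment/registration (Overview, 1, 6, 7-1) | counted | outside mITT |
| Onset (14-3) | counted, if within 14 days of onset | outside mITT |
| Surgery (8, rupture and hemorrhagic stroke) | not counted | outside mITT |

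The ISTH list in section 8 carries no surgery limit, so an intracranial bleed excluded as a stroke event could still be claimed as a major bleed.

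**2. The plan's own figure.** No power or event rate is stated for the bleeding test. The sample size in section 14-2 rests on the primary endpoints (15% vs 5%, two-sided 2.5%, 90% power, 230 per arm). It reproduces: at 230 per arm, power is 91.2% by the normal approximation and 90.2% by exact enumeration of Fisher's test. I use 230 per arm below.

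**3. Model.** Let r be the share of dosed patients in each arm with a qualifying pre-dose bleed, b the post-dose placebo risk, and d the true post-dose excess on aspirin. Post-dose risk is taken as independent of a pre-dose bleed.

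- Placebo rate: p0 = r + (1 − r)b
- Aspirin rate: p1 = r + (1 − r)(b + d)
- Observed difference: p1 − p0 = (1 − r)d
- SE = √[p0(1 − p0)/230 + p1(1 − p1)/230]
- P(non-inferiority) = Φ[(0.10 − (p1 − p0))/SE − 1.96]

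The values of r and b are assumptions; the documents give neither.

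**4. One case in full: b = 10%, r = 5%.**

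- True excess at the margin (d = 10 points): p0 = 0.05 + 0.95 × 0.10 = 0.145; p1 = 0.05 + 0.95 × 0.20 = 0.240; difference 0.095; SE 0.0365. Then 0.005/0.0365 − 1.96 = −1.82, so P = 3.4%.
- No excess (d = 0): p0 = p1 = 0.145; SE 0.0328. Then 0.10/0.0328 − 1.96 = 1.09, so P = 86.1%.

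**5. Range, b = 10%.**

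| r | Observed excess when true d = 10 | False non-inferiority | Power when d = 0 |
|---|---|---|---|
| 0% | 10.0 | 2.5% | 94.7% |
| 1% | 9.9 | 2.7% | 93.1% |
| 2% | 9.8 | 2.9% | 91.4% |
| 5% | 9.5 | 3.4% | 86.1% |
| 10% | 9.0 | 4.4% | 78.0% |

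**6. Sensitivity to b.** For b = 5% to 15% and r = 2% to 10%, false non-inferiority lies between about 2.8% and 4.6%. Power with no excess is 99.8% to 85.2% at r = 0 and 86.1% to 71.5% at r = 10%. Counting only from dosing is the r = 0 case.

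**The case against.** **The event definitions already exclude these events.** Section 8 limits rupture and hemorrhagic stroke to the period after surgery. This is the strongest point, and it stands in part: a reader might infer that every re-rupture before the drug counts, and the documents do not support that. It does not close the matter, because section 7-1 is the endpoint definition and names registration, section 14-3 names onset, and the ISTH list has no surgery limit.

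**Undosed patients drop out.** This is correct. A re-rupture that ends in cancelled surgery never reaches the test; only bleeds in patients later dosed are at issue. Section 7-1 also requires bleeds to be symptomatic or ISTH-major, so minor drainage bleeds do not qualify.

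**Blinded randomization balances pre-dose bleeds.** This also stands. A reader might infer a bias toward one arm, but neither the bleeds nor a cancellation before dosing can depend on a drug not yet given.

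**The wait may be short.** The 72 h run from onset to embolization, not from allocation to dose, and neither the gap nor the pre-dose bleeding rate is given. The registration steps in section 6-4 are compatible with a short gap. The size is therefore conditional.

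**Counting from randomization is a recognized choice.** It is, in an analysis of all randomized patients. Here the set is already limited to dosed patients, so an earlier clock brings no such completeness.

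**Conclusion.** The protocol contradicts itself on when the bleeding window opens. Under the enrollment and onset readings, the non-inferiority test takes in bleeds that precede the only dose, for the subset of patients who are later dosed. The consequence is dilution and added variance.

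With 230 per arm, 10% post-dose bleeding on placebo and 2–5% pre-dose bleeding in both arms (both rates assumed), false non-inferiority at a true 10-point excess is about 2.9–3.4% instead of 2.5%, and power with no excess is about 91–86% instead of 94.7%. At 1–2% the change is small.

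Two stronger inferences are not supported. One is that a 1% pre-dose rate turns a pass into a failure. With post-dose risks of 5% and 10%, the expected upper limit does move from 9.8 to 10.0 points, but that case sits on the margin by construction, with about a 53% chance of passing even without pre-dose bleeds. The other is that undosed patients use up the roughly 5% dropout allowance; the protocol gives no never-dosed rate from which to conclude this.

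The point deserves correction because the rule is the only formal bleeding decision and the contradiction is plain in the text, not because a large error has been shown.

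**What to change.** 1. State one window for the mITT non-inferiority test: bleeding with onset from study-drug administration to 14 days after it. Where the dose time is unavailable, use the sheath insertion time, which section 8 already records to the minute. Apply the same wording in the Overview, section 1, section 6 (postoperative management), section 7-1, the stroke and bleeding definitions in section 8, and section 14-3.
2. List bleeds between allocation and dosing separately, by arm, for all randomized patients, including those never dosed. No safety information is then lost.
3. Add two items to the case report form: the time of dosing, and a clock time for any bleed on the day of surgery. The section 8 event form records only a date and the surgical items list no dose time, so a bleed before the dose could not otherwise be told from one after it on the same day.

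The cost is an amendment of wording and two data fields. Slightly fewer events may enter the test. The timing of allocation need not change; a later allocation step would be a workflow preference, and this point does not depend on it.
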